#### MHWC referral activities log and job analysis

To evaluate the tasks, responsibilities, time, and resources required to achieve all aspects of the MHWC role and successful implementation of the MHWC model, MHWC activity will be recorded in a study developed database. This information will include number of students impacted, number of interactions with classroom teachers, time spent on tasks, type of mental health and wellbeing activities the MHWC is assisting with, number of referrals made, uptake/outcome of referral, waitlist times, number, and type of interactions with regional staff. This information will be collected for two working weeks during the academic school year (Semester 2).

#### Feasibility, appropriateness, and acceptability of the MHWC model

To evaluate the feasibility, appropriateness, and acceptability of the MHWC model we will use the Feasibility of Intervention Measure (FIM), Intervention Appropriateness Measure (IAM) and the Acceptability of Intervention Measure (AIM) [50] adapted as required. These measures will assess the extent to which a new treatment or innovation can be successfully used or carried out within a setting (FIM), the perceived fit, relevance and compatibility of the intervention for a given practice setting, provider, or consumer and/or perceived fit of the innovation to address a particular issue or problem (IAM) and the perception among implementation stakeholders that an intervention is agreeable or satisfactory (AIM). These measures consist of 4-items each targeting perceived intervention acceptability. Items are measured on a 5-point Likert scale (completely disagree-completely agree) and the score is a calculated mean. Each measure has excellent structural validity (FIM α = 0.89, IAM α = 0.91, AIM α = 0.85) and test-retest reliability (FIM α = 0.88, IAM α = 0.87, AIM α = 0.83) [50].

#### Engagement of school staff with MHWC model

To evaluate the level of engagement that school staff have with the MHWC model, questions will be developed to capture the perceived level of engagement required, the actual level of engagement and the types of support provided to staff by MHWCs.

#### Focus groups

To further explore and capture data regarding the feasibility, appropriateness, and acceptability of the model, purposive sampling will be used to recruit a subset of school and regional staff to participate in qualitative focus groups at T4 and T5, using a semi-structured interview guide. Focus groups will consist of between 3 and 8 participants and will include MHWCs and other trainees from participating intervention schools as well as a cross-section of other school staff (including leadership and education support staff, wellbeing staff, classroom teachers) and regional support staff. Interviews will be facilitated by an experienced qualitative researcher, audio-recorded with permission from the participants and transcribed verbatim using an external transcription service.

### Moderators

Exploration of potential moderators to the relationship between the intervention and the primary outcome will include planned FTE allocation of MHWC, socio-economic status (ICSEA value), school geographic location (metro/rural/regional), as well as process moderators; training dosage (hours attended of training) and local adjustments to MHWC FTE by the school during implementation (average hours worked in MHWC role).

### Sample size calculation

We based the sample size calculation on the primary study objective of detecting the impact of the MHWC model on classroom teachers’ self-reported confidence to support student mental health and wellbeing which is assessed by the School Mental Health Self-Efficacy Teacher Survey (SMH-SETS [55]). We assumed a mean SMH-SETS score of 67.7 (standard deviation = 9.5) in the BAU arm based on unpublished data provided by the measure authors [56]. Participation of 12 teachers per school with the intra-cluster (intra-school) correlation coefficient (ICC) set to 0.1 (expected ICC is unknown); the sample of 32 schools (16 intervention schools and 16 BAU schools) provides 80% power at the (2-sided) 5% level of significance to detect a mean difference between the trial arms of 3.9 on the teacher-reported SMH-SETs score.

### Planned statistical analysis

All analyses will be based on observed data only; i.e. we will assume data are Missing Completely At Random. We will make every attempt to ensure that data are not missing from surveys at the point of completion. If there are missing responses to surveys completed by school or regional staff, we will follow up via phone or email up to three times to obtain the missing responses. If missing data are > 10% for specific outcomes, then predictors of missing data will be explored and sensitivity analyses making further adjustments (i.e. valid under Missing At Random) will be used such as imputation. The details of how this will be conducted will be outlined in the statistical analysis plan.

The primary outcome (mean difference in SMH-SETS total score) will be analysed using mixed effects linear regression fitted at the teacher level, including a fixed effect for arm (MHWC vs. BAU) and a random effect for school, adjusting for baseline values of SMH-SETS and school matching criteria (ICSEA, number of enrolments and metro/regional/rural location).

According to the nature of the secondary outcomes to be analysed (binary, continuous or ordinal) the appropriate mixed effects model will be used to estimate the impact of the MHWC model on the outcome of interest compared to the BAU schools. These models will be fitted at the participant level, including a fixed effect for arm (MHWC vs. BAU) and a random effect for school adjusting for school matching criteria (ICSEA, number of enrolments and metro/regional/rural location) and baseline value of the outcome where available. Analyses will be done using Stata Statistical Software MP.

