#### Years 2 and 4 classroom teachers and parents/carers

Across both intervention and BAU schools, parents/carers of students from years 2 and 4 (ages 7–8 and 9–10) will receive an email from the principal (T2) inviting them to (a) consent to information being collected about their child by the classroom teacher and (b) complete an online survey at two timepoints (see Fig. 1). Parents/carers must be the primary caregiver of a student from one of the selected year levels. Classroom teachers from years 2 and 4 will subsequently receive an email from the principal (T3) inviting them to complete the Strengths and Difficulties Questionnaire [52] on each child in their class for whom parental or carer consent has been obtained (see Fig. 1  and Table 2). Parents/carers and teachers will be asked to complete an online consent form, including the relevant plain language statement before completing the survey (Table 1).

**Table 1 Tab1:** Summary of participant groups and projected number of participants in each group

Participant group		Number of participants	
		Intervention schools	BAU schools
MHWC and other trainees	MHWC	16 (1 per school)	–
	Training participants	48 (3 per school)	–
School staff	Classroom teachers^a^	192 (12 per school)	192 (12 per school)
	Education Support Staff	32–48 (at least 2 per school)	32–48 (at least 2 per school)
	School leadership (principal, APs, leading teachers, wellbeing)	32–48 (at least 2 per school)	32–48 (at least 2 per schools)
Parents/carers	Parents/carers from years 2 and 4	496 (31 per school)	496 (31 per school)
Year 2 / Year 4 classroom teachers	Classroom teachers from years 2 and 4	64 (2 classrooms per year level per school)	64 (2 classrooms per year level per school)

^a^ Primary outcome will be measured within this participant group. See further details under Sample Size Calculation

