#### Prioritisation of student mental health

To evaluate the level of prioritisation of child mental health and wellbeing, school leaders will answer questions exploring the level of priority given to wellbeing and mental health provision for students, whether wellbeing and mental health provision for students is part of the school strategic plan or annual implementation plan, or if the school has a policy related to child mental health and wellbeing.

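### The plan and policy items of the prioritisation outcome have one true value per school, so the participant-level mixed model fixed for secondary outcomes can give them an uninterpretable odds ratio

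*Protocol article*

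**What the plan says.** Planned statistical analysis lets the type of mixed model follow the scale of each secondary outcome (binary, continuous or ordinal), but it fixes the level: "These models will be fitted at the participant level, including a fixed effect for arm (MHWC vs. BAU) and a random effect for school". Adjustment is for the school matching criteria and, where available, the baseline value. No secondary outcome is exempted, and there is no rule for reducing several answers from one school to a single value.

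The subsection on prioritisation of student mental health names school leaders as respondents and lists two kinds of question. One is a perception: how much priority the school gives to provision. The others are facts: whether provision "is part of the school strategic plan or annual implementation plan, or if the school has a policy related to child mental health and wellbeing".

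Table 1 has a row for "School leadership (principal, APs, leading teachers, wellbeing" and projects 32–48 people per arm in it, at least 2 per school. Table 2 lists prioritisation among the secondary outcomes, measured at T1, T5 and T6.

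**The concern.** A school either has a policy at a given time or it does not, and the same holds for its strategic and annual plans. Two or three leaders of one school are reporting the same fact, so their answers should mostly coincide. A random-intercept logistic model needs variation within schools to estimate the school standard deviation (SD), and the conditional odds ratio for arm is scaled by that SD. With little or no variation within schools, the SD and the odds ratio grow together.

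At stake is the reported effect on part of a named secondary objective (systemic factors). The output could be a failed fit, or an odds ratio and interval that say little about how many schools have a policy.

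**Working it through.** **The plan's own figure.** The only computed figure is for the primary outcome. Inputs from Sample size calculation: "We assumed a mean SMH-SETS score of 67.7 (standard deviation = 9.5) in the BAU arm"; "Participation of 12 teachers per school with the intra-cluster (intra-school) correlation coefficient (ICC) set to 0.1"; 16 schools per arm.
- Design effect: 1 + (12 − 1) × 0.1 = 2.1.
- Effective n per arm: 16 × 12 / 2.1 = 91.4.
- SE: 9.5 × √(2/91.4) = 1.405.
- Detectable difference: (1.960 + 0.842) × 1.405 = 3.94, and power at 3.9 is 0.793.

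This agrees with the statement that the sample "provides 80% power at the (2-sided) 5% level of significance to detect a mean difference between the trial arms of 3.9". The present point does not affect it.

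**Inputs for the check.** From the protocol: 16 schools per arm; two to three leaders per school (32/16 to 48/16); participant-level model with a school random intercept. Assumed, because the protocol does not give them: yes/no items, a logit link, and yes in 12/16 intervention and 8/16 business-as-usual schools. Baseline value and matching covariates are left out.

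**One row per school.**
- Log odds ratio: ln(12/4) − ln(8/8) = 1.10, so the odds ratio is 3.0.
- SE: √(1/12 + 1/4 + 1/8 + 1/8) = 0.76.
- Likelihood-ratio statistic: 2.16.
- Risk difference: 0.75 − 0.50 = 0.25, SE 0.171.

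**Participant level, three leaders, full agreement.** The likelihood was maximised over the intercept and arm effect at each fixed school SD, integrating over the school effect on a fine grid:

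| School SD | Log OR | Log-likelihood | LR statistic |
|---|---|---|---|
| 1 | 1.39 | −48.2 | 5.13 |
| 5 | 3.94 | −27.4 | 3.01 |
| 10 | 7.26 | −23.7 | 2.58 |
| 50 | 34.2 | −20.8 | 2.25 |
| 100 | 67.9 | −20.4 | 2.21 |

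The log-likelihood keeps rising with the SD, so there is no finite maximum. The reason can be seen directly. When all answers in a school agree, that school's contribution tends, as the SD grows, to the normal probability of the linear predictor divided by the SD. The limit of the log-likelihood is the school-level value, 12 ln 0.75 + 4 ln 0.25 + 16 ln 0.5 = −20.09. The log odds ratio then grows as SD × (0.674 − 0), where 0.674 and 0 are the normal quantiles of 0.75 and 0.50; at SD 100 this is 67.4, close to the 67.9 found. The pattern is the same with 2, 5 or 17 respondents per school.

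**Three leaders, some disagreement.** Discordant schools in each arm were split equally between two-of-three yes and one-of-three yes. The share of yes answers stays at 0.75 and 0.50. For example, with four discordant schools per arm it is (10×3 + 2×2 + 2×1)/48 = 36/48 against (6×3 + 2×2 + 2×1)/48 = 24/48. The odds ratio from those shares is therefore always 3.0. The mixed-model results are:
- 4 discordant schools per arm: OR 18.2 (school SD 3.93).
- 2 per arm: OR about 330 (SD 8.42).
- 1 per arm (half a school's weight on each pattern): OR about 100,000 (SD 17.1).

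**Linear mixed model.** The estimate stays at 0.25. With slight noise added its SE is 0.171, as at school level. Under exact agreement the residual variance is zero and the software fit is degenerate (reported SE 0.119 with two leaders, 0.096 with three).

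**The case against.** **Detail for the statistical analysis plan.** The article is condensed, and scoring of purpose-built items and the choice of link are commonly settled in the analysis plan, which is not shown. That stands for scoring and link. It does not cover the level of analysis, which the article states for secondary outcomes without exception.

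**The premises are assumed.** The article gives no response format, does not say whether the items are analysed singly or combined, and does not report how far leaders agree. This stands, and the conclusion is conditional on it. Divergence under full agreement does not depend on the assumed rates.

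**Conditional and marginal odds ratios differ anyway.** True: part of the gap between 3.0 and 18 is the ordinary difference between the two, which widens with the school SD. But here the SD reflects how often leaders contradict each other about a fact, so the conditional figure has no useful interpretation.

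**A reader might infer false precision**, since three leaders of one school enter as three records. The documents do not support this. The random effect is in the plan, and as the school SD grows the likelihood-ratio statistic falls to 2.21, against 2.16 with one row per school. In a small simulation (120 runs per scenario) under no effect and full agreement, the test rejected in 5.8% of runs, the same as the school-level test. The SE would be too small only if the school effect were dropped (0.54 with two leaders, 0.44 with three, against 0.76), or if a degenerate or prematurely stopped fit were accepted.

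**A reader might also infer that misreporting by leaders creates the effect, or that the whole outcome fails.** Neither follows. More disagreement brings the odds ratio down towards a finite value, and the perceived level-of-priority item varies between respondents and suits the planned model.

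**Conclusion.** The point holds for the plan and policy items only. The protocol sets a participant-level model for items with one true value per school. Analysed as yes/no in a random-intercept logistic model, they would give a divergent odds ratio if leaders agree, or one that depends on the amount of disagreement if they nearly agree: about 18 rather than 3.0 with four discordant schools per arm under the assumed rates. The size rests on those rates, on the yes/no format and on high agreement, none of which the protocol states.

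The test of the arm effect is roughly preserved, so the loss is an interpretable effect size and interval, or a converged fit. An analyst would probably notice. The primary outcome, the perceived-priority item and the other seven secondary-outcome rows in Table 2 are not affected by this point. Severity: minor.

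**What to change.** For the plan and policy items only, state in the protocol or analysis plan that:
- one value per school and timepoint is derived by a pre-specified rule for conflicting answers, for example the principal's answer, otherwise another leader's;
- arms are compared at school level (32 rows) with a risk difference or a small-sample method such as penalised logistic regression;
- the participant-level mixed model is kept for the perceived level-of-priority item.

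This is a change of wording and needs no new data. The downside is small: with 32 rows fewer covariates can be adjusted for, so the matching criteria and baseline value to be retained should be named in advance.

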### Cost analysis

Variation in costs across participating schools will be evaluated to identify factors that may impact on the costs of delivering the intervention according to school characteristics such as number of student enrolments, location, and SES. Based on these estimated costs, budget impact of delivering the intervention state-wide will be calculated, with associated resource implications, particularly workforce.

### Qualitative analysis

Focus group transcripts will be deidentified and imported into the computer software package QSR Nvivo 12 [57]. Data analysis will follow the guidelines for reflexive thematic analysis [58]. An experienced qualitative researcher will independently code the data and emergent categories and themes will be cross-checked with the broader team for accuracy and to ensure the data is well represented. Study findings will be reported in line with the COREQ checklist for reporting qualitative research [59].

## Discussion

This study protocol introduces a quasi-experimental cluster study investigating the impact of a mental health and wellbeing coordinator (MHWC) model on classroom teacher confidence to support student mental health and wellbeing in an Australian primary school setting. Previous approaches have largely focussed on developing and evaluating specific mental health and wellbeing programs delivered using existing school resources in cross-sectional study designs with limited attention paid to implementation factors [38]. This protocol describes a novel approach to building the capacity of primary schools by introducing an additional resource for schools, the MHWC, which is embedded through an implementation science framework to maximise impact on target outcomes and long-term sustainability.

Despite the strengths of the proposed study, there are some practical limitations involved in conducting applied research in a school setting [60]. First, a randomised controlled trial (RCT), the gold standard for assessing effectiveness of an intervention, was not feasible in the current study as intervention schools were selected by DET based on mental health need, readiness and context diversity [61]. The quasi-experimental design does have the benefit of enabling enrolment of schools to the intervention based on motivation, which reflects the real-life situation of public health interventions. The lack of randomisation, however, can introduce both selection bias and confounding. We will aim to mitigate these biases by matching our control schools and adjusting for known confounders as well as T1 values at the analysis level.

Second, standardised measures and data collection methods for some of the project outcomes were not available (i.e., Mental Health Literacy [62], routine collection of outcomes (e.g. referral data)). Ideally standardised measures and data collection processes would be used to maximise the quality of the research conclusions, including comparisons with previous school-based mental health initiatives, and across intervention and BAU schools. This lack of measures relevant to the study outcomes and standardised processes for routine data collection in schools likely reflects a historical lack of scientific rigour in evaluating school-based initiatives [63]. To mitigate the lack of appropriate measures, the research team in collaboration with an expert advisory panel, developed bespoke items to target these outcomes. The measures developed for this project will likely be relevant for future projects and therefore measures development may form a sub-project of the broader study. To mitigate the lack of standardised, routine data collection across schools, the research team has developed data collection templates that will capture pertinent referral pathway information for students. Due to the absence of routinely collected resource or cost data on mental health supports in schools, it is not possible in this study to compare the costs in intervention and BAU schools, so the full cost implications of the model will not be estimated, nor will an economic evaluation that compares costs and outcomes between intervention and BAU schools be conducted.

Finally, there are additional context considerations in the state of Victoria in 2021 that will need to be taken into account during data analysis and interpretation. These include the acute and longer-term impacts of the COVID-19 pandemic, school closures and remote learning on the mental health of students, teachers and the education community [64, 65] as well as the resources and programs being implemented by individual schools following the findings and recommendations of the Royal Commission into Victoria’s Mental Health System in March 2021 [66]. The COVID-19 pandemic is a fluid situation, so that a comprehensive risk mitigation strategy has been developed to plan for various situations as they arise (e.g., higher than anticipated attrition rate for schools and participants, schools returning to remote learning and the MHWC role and training being implemented using teleconferencing methods). In contrast, the findings from the Royal Commission are static, but may have longer-term, permanent implications for the offerings provided by schools to better support student mental health. To mitigate this, a comprehensive list of actions taken in response to the Royal Commission recommendations will be collected for each school and taken into account when interpreting data from the proposed study.

Results from this study will inform decision-making around large-scale mental health service reform and possible state and national roll out of the intervention [66]. To ensure the ongoing quality and sustainability of the MHWC model should it prove to be efficacious, it is imperative that there is ongoing monitoring and evaluation of the model is conducted. This would involve follow up of primary and secondary outcomes as well as implementation factors associated with the MHWC model including identification of enablers and barriers across school, region/district and system levels [43]. This design will address some of the shortcomings of previous approaches to address child mental health issues in primary schools and maximise the likelihood that the MHWC intervention will have positive long-term, sustainable effects on child mental health. This approach will not only impact the individual child and their family, but benefits may also be seen at a community and societal scale, across education and health sectors, and likely be experienced by generations to come.

## Data Availability

Not applicable.

## Abbreviations

ACMHQ: Attitudes about Child Mental Health Questionnaire
AIM: Acceptability of Intervention Measure
AToSS: Attitudes to School Survey
BAU: Business of Usual
FTE: Full-Time Equivalent
ICSEA: Index of Community Socio-Educational Advantage
MHWC: Mental Health and Wellbeing Coordinator
NW: North-West
POS: Parent Opinion Survey
RCT: Randomised Control Trial
SES: Socio-Economic Status
SQD: Strengths and Difficulties Questionnaire
SMH-SETS: School Mental Health Self-Efficacy Teacher Survey
SW: South-West
